### Study setting

The study is supported by the Department of Rehabilitation Medicine, Yueyang Hospital, Shanghai University of Traditional Chinese Medicine. All interventions will be conducted in the Department of Rehabilitation Medicine, Yueyang Hospital, Shanghai University of Traditional Chinese Medicine.

### Recruitment and sample selection

Subjects will be recruited by the Department of Rehabilitation Medicine, Yueyang Hospital, Shanghai University of Traditional Chinese Medicine,based on strict inclusion and exclusion criteria. Those who meet the criteria will be asked to sign an informed consent form.

### Inclusion criteria

Stroke (Infarction/Ischemia) [40];Age ≥ 40 years and ≤ 70 years, regardless of sex [41];Time of onset ≥ three months and ≤ 1 year;right-handedness;normal cognitive function (MMSE above the threshold corresponding to different cultural levels);Informed consent;

### Exclusion criteria [42]

Contraindicated implants for MRI and TMS in vitro and in vivo;History of epilepsy, psychiatric disorders, or other serious cognitive or emotional disorders;History of medications that affect the central nervous system;Pregnant or lactating women;

### Dropout criteria

Withdrawal from the study;Incomplete implementation of the treatment plan;Other treatment access;Blinding failure;

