**Fig. 1 Fig1:**
[figure not shown]
Flow diagram of study design. ccPAS, Cortical-cortical paired associative stimulation; FMA-UE, Fugl-meyer assessment of upper extremity; MTCF, Modified Taylor Complex Figure; NIHSS, National Institutes of Health Stroke Scale; fMRI, functional Magnetic Resonance Imaging; DTI, Diffusion tensor imaging

**Table 1 Tab1:** Participant timeline

Activity			Study Stuff		Study Period						
				Prestudy	0 week	1 week	2 weeks	2 weeks end	6 weeks end	10 weeks end	
Preparation	Sample size calculation		Investigator A	X							
	Eligibility screen		Investigator B	X		X	X	X	X	X	
	Medical information		Investigator B	X							
	Informed consent		Investigator B	X							
	Random allocation		Investigator B	X							
Intervention	ccPAS Low frequency Group	Conventional therapy	Doctor B + Therapist			X	X				
		0.2 HZ ccPAS	Investigator C			X	X				
	ccPAS High frequency Group	Conventional therapy	Doctor B + Therapist			X	X				
		5 HZ ccPAS	Investigator C			X	X				
	control Group	Conventional therapy	Doctor B + Therapist			X	X				
		sham-ccPAS	Investigator C			X	X				
Assessment	Primary outcome	FMA-UE	Assessor A		X			X	X	X	
	Secondary outcomes	The Line bisection test	Assessor B								
		MTCF	Assessor B		X			X	X	X	
		NIHSS	Assessor B		X			X	X	X	
		fMRI	Imaging doctor		X			X	X	X	
		DTI	Imaging doctor		X			X	X	X	
Statistical analysis			Investigator A					X		X	

ccPAS, Cortical-cortical paired associative stimulation; FMA-UE, Fugl-meyer assessment of upper extremity; MTCF, Modified Taylor Complex Figure; NIHSS, National Institutes of Health Stroke Scale; fMRI, functional Magnetic Resonance Imaging; DTI, Diffusion tensor imaging.

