### Sample size calculation

In this study, the sample size was determined using a multiple group mean comparison method. The sample calculation formula is $$n = {\varphi ^2}\left( {\sum {S_i^2/g} } \right)/\left[ {{{\sum {\left( {{{\bar X}_t} - \bar X} \right)} }^2}/\left( {g - 1} \right)} \right]$$

The number of groups(g) is three, and the number of participants in the control and ccPAS low-frequency groups and the ccPAS high-frequency group was 1:1:1. α is the probability of rejecting a true null hypothesis, α is set to 0.025. β is set to 0.1, power(1-β) is the probability of rejecting a false null hypothesis. K is the group means multiplier; k is 1. The value of φ is obtained by checking the table according to α, β, v1, v2.According to previous studies, the three group means are set to 8.11 6.87 17.62, the within group standard deviation (σ) is 8.83 [43]. Using PASS 15 analysis, we get that the total sample size is 54 and the sample size of each group is 18. Considering the 20% dropout rate, the total sample size of the study should be set to 69 and the sample size of each group is 23.

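### Incomplete treatment, other treatment and blinding failure are dropout criteria, so following the text can lose randomised patients for reasons related to arm and outcome

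*Protocol article*

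**What the plan says.** The Dropout criteria section of the protocol article is one list: "Withdrawal from the study;Incomplete implementation of the treatment plan;Other treatment access;Blinding failure". It does not say who applies the criteria, whether visits stop, or what happens to data already collected.

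The Sample size calculation section first finds that "the total sample size is 54 and the sample size of each group is 18". It then adds: "Considering the 20% dropout rate, the total sample size of the study should be set to 69", that is, 23 per group.

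Table 1 places random allocation in the pre-study column. It marks the row "Eligibility screen" before the study and again in weeks 1 and 2, at the end of treatment and at both follow-ups. The FMA-UE is scheduled at baseline, at the end of treatment and at both follow-ups.

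The Behavior statistical analysis section uses repeated-measures ANOVA or the Friedman test within groups, and one-way ANOVA or the Kruskal-Wallis test between groups. It names no analysis set.

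The Discontinuation criteria section separately covers other diseases and serious adverse reactions, by joint decision of subject and investigator.

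**The concern.** Withdrawal is a real loss of contact. The other three items are not: a patient who missed sessions, had other therapy or guessed the allocation can still be scored on the FMA-UE. If such patients are dropped, the remaining groups are no longer those that randomisation formed.

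Each event can plausibly depend on arm and outcome:

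- **Blinding failure.** High-frequency sessions take 3.6 min and low-frequency sessions 15 min, and sham otherwise follows the low-frequency parameters. Session length can therefore reveal the high-frequency arm. A felt response can also prompt a guess.
- **Incomplete treatment.** Poor tolerance or lack of benefit can lead to missed sessions.
- **Other treatment.** Patients who see no progress may look elsewhere.

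The primary between-arm FMA-UE comparison is at stake, in a trial with about 20 patients per arm. If dropout ends assessment, no later choice of analysis set can recover the unmeasured outcomes.

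**Working it through.** **Inputs from the Sample size calculation section.** "α is set to 0.025"; "β is set to 0.1"; "the three group means are set to 8.11 6.87 17.62"; "the within group standard deviation (σ) is 8.83"; three equal groups; 20% dropout. The article does not label the means by arm. I read them in the order in which that section names the arms: control, low frequency, high frequency.

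**Step 1: reproduce the plan's figures.** The grand mean is (8.11 + 6.87 + 17.62)/3 = 10.867. The squared deviations are 7.60 + 15.97 + 45.61 = 69.18. With 18 per group the noncentrality is 18 × 69.18 / 8.83² = 15.97. The one-way ANOVA F test with 2 and 51 degrees of freedom at 0.025 then has power 90.2%, and 18 is the smallest group size that reaches 90%. For dropout, 18/(1 − 0.20) = 22.5, rounded up to 23 per group, or 69 in total. Both stated figures reproduce, so the arithmetic is sound. The inflation only makes sense if a dropout contributes nothing to the analysis.

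**Step 2: how many patients.** 23 − 18 = 5 per arm (22%), or 15 of 69.

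**Step 3: shift in one arm's mean.** Suppose a fraction d = 5/23 = 0.217 leaves one arm, and the process behind leaving has correlation r with a poor result. For a normal outcome the mean of those kept rises by r × SD × φ(z)/(1 − d), where z is the d-quantile. Here z = −0.781 and φ(z) = 0.294, so 0.294/0.783 = 0.376 SD, and 0.376 × 8.83 = 3.32 points at r = 1. The planned difference is 17.62 − 8.11 = 9.51.

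| Assumed r | Shift (points) | Share of 9.51 |
|---|---|---|
| 0.25 | 0.83 | 9% |
| 0.5 | 1.66 | 17% |
| 1.0 (ceiling) | 3.32 | 35% |

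**Step 4: effect on type I error.** The simulation assumed no true difference and SD 8.83, with 18 of 23 kept in each arm. Removal was random in two arms and outcome-related in the third. There were 40,000 runs at nominal 5%.

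| Assumed r | Mean shift (points) | Type I error |
|---|---|---|
| 0 | 0.0 | 5.0% |
| 0.3 | 1.0 | 6.0% |
| 0.5 | 1.6 | 8.3% |
| 1.0 | 3.2 | 21% |

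The simulated shifts are slightly below the formula because each arm has only 23 patients.

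**Step 5: does keeping everyone gain power?** This takes high frequency against control, two-sided 0.025, with pooled degrees of freedom. Power is 81.8% with 18 per arm and 91.0% with 23, if the patients kept have the full effect. With an assumed dilution of 10% or 20% in all 23, it is 83.7% or 73.4%. If 5 of 23 gain nothing (the difference shrinks to 18/23), it is 71%, below the 81.8% for 18 full adherers.

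**The case against.** The strongest objection is that the key step is not written down. The dropout list has no verb, and no section says that visits stop or that data are left out. Analysis sets are commonly defined in a full protocol or SAP, neither of which is shown. A 20% allowance is also ordinary, and the article does not say which of the four events it covers. This stands: exclusion is an inference from the label, from the inflation of 54 to 69, and from within-group tests that, as usually run, need complete cases. It does not remove the point. The article itself states the list, and if dropout ends assessment, an as-randomised set defined elsewhere would have outcomes missing.

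The bias is also uncertain in size and direction. The 3.3-point shift needs the five worst patients to leave one arm, with no outcome-related loss elsewhere. Sham patients without benefit may leave too, which would offset it. That stands, so 3.3 is a ceiling and not an expected value.

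A reader might infer two further things that the documents do not support:

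- **That the repeated eligibility screens remove patients.** Nothing says that failing a later screen removes anyone. The marks fall in the stimulation weeks and at visits with MRI, so they may be checks for contraindications.
- **That the three items are all imposed by the investigator.** The list does not say who applies them, and missing sessions or seeking other treatment can be the patient's own act.

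**Conclusion.** The point holds as a correction to the dropout rule. As written, the article classes three post-randomisation events as dropout, and its sample size treats dropouts as giving no data. Those events can differ by arm and relate to outcome, so losing these patients can bias the FMA-UE comparison.

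The size cannot be derived from the document. Under assumed correlations of 0.25 to 0.5, with outcome-related loss in one arm only, the shift is 0.8 to 1.7 points, or 9% to 17% of the planned difference. Type I error in the simulation is 6.0% at a correlation of 0.3 and 8.3% at 0.5. These rest on a normal outcome with SD 8.83 and 5 of 23 lost.

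It would go too far to say that the trial has abandoned its randomised comparison, because the article does not state the exclusion. It would also go too far to promise more power from keeping everyone, since that gain can vanish once non-adherers dilute the effect. The case for keeping them rests on bias.

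**What to change.** 1. Reclassify incomplete treatment, other treatment and blinding failure as protocol deviations, recorded by arm with date and reason.
2. State that the already scheduled outcome assessments continue after these events, unless the patient withdraws from follow-up.
3. Make the comparison of all randomised patients in their assigned arms primary. Use the present list only to define a secondary per-protocol set.
4. Keep the repeated eligibility marks in Table 1, and state that they do not remove patients from the analysis.
5. Reconcile this wording with the Discontinuation criteria section, so that stopping treatment and stopping outcome assessment are distinguished. Which clinical rule applies is for the investigators to decide.

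The cost is mainly wording, plus assessing patients whose visits are already scheduled. The downside is some dilution of the effect from non-adherers. The sample size text should therefore not claim a power gain from the patients kept.

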**Method:**

This study is a randomized, double-blind controlled clinical trial over a 14-week period. 69 stroke subjects will be enrolled and divided into sham stimulation group, ccPAS low frequency group, and ccPAS high frequency group. All groups will receive conventional rehabilitation. The intervention lasted for two weeks, five times a week. Assessments will be performed before the intervention, at the end of the intervention, and followed up at 6 and 14 weeks. The primary assessment indicator is the ‘Fugl-Meyer Assessment of the Upper Extremity ’, secondary outcomes were ‘The line bisection test’, ‘Modified Taylor Complex Figure’, ‘NIHSS’ and neuroimaging assessments. All adverse events will be recorded.

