## Methods and analysis

### Study design

This study is a double-blind randomized controlled trial, and the protocol is registered with the Chinese Clinical Trials Registry. A total of 69 participants will be divided 1:1:1 into three groups. The control group will receive conventional treatment plus sham ccPAS, the ccPAS low-frequency group received conventional treatment plus 0.2 HZ of ccPAS, and the ccPAS high-frequency group will receive conventional treatment plus 5 HZ of ccPAS.

Each group will receive the intervention five times per week for two weeks. The researcher will follow up with subjects in week six and week fourteen respectively (as shown in Fig. 1 and Table 1).T The primary outcome measure will be the ‘Fugl-Meyer Assessment of the Upper Extremity (FMA-UE)’, secondary outcomes will include ‘The line bisection test’, ‘Modified Taylor Complex Figure (MTCF)’, ‘NIH stroke scale (NIHSS)’, and’ functional Magnetic Resonance Imaging(fMRI)’ as well as ‘Diffusion tensor imaging (DTI)’.

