### Discontinuation criteria

If a patient develops other diseases or experiences serious adverse reactions during treatment, the trial will be discontinued at the mutual decision of the subject and the investigator.

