### Intervention

Subjects will receive regular rehabilitation, including physiotherapy, occupational therapy, and speech and language therapy. Brain areas will be localized using the LOCALITE TMS Navigator system, which will rely on the patient’s magnetic resonance structural images to localize the M1 and V1 [44]. Patients will receive ccPAS treatment with a MagTD magnetic field stimulator from Wuhan Iredell Medical Equipment New Technology Co.

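### Receiving other treatment is a dropout reason with no time limit, so randomised patients who could still be assessed may be lost from the FMA-UE comparison, especially at the two later visits

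*Protocol article*

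**What the plan says.** The Dropout criteria section of the protocol article is a list of four reasons: withdrawal, incomplete delivery of the treatment plan, "Other treatment access", and failure of blinding. The third has no period attached, and what counts as other treatment is not defined. The section that follows, Discontinuation criteria, does name a period: it concerns a patient who develops other diseases or "experiences serious adverse reactions during treatment".

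The intervention lasts two weeks, and the Study design section says the researcher will "follow up with subjects in week six and week fourteen respectively". Table 1 schedules FMA-UE, the primary outcome, at baseline, at the end of the intervention and at both follow-up visits.

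On background care, the Abstract says "All groups will receive conventional rehabilitation", and the Intervention section says "Subjects will receive regular rehabilitation, including physiotherapy, occupational therapy, and speech and language therapy". Neither gives an end date. Table 1 marks "Conventional therapy" in weeks 1 and 2 only.

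The Sample size calculation section reaches 54 patients and then adds: "Considering the 20% dropout rate, the total sample size of the study should be set to 69".

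**The concern.** Withdrawal is already on the list. The separate entry for other treatment therefore reaches patients who have not withdrawn and could still attend. Whether they obtain other treatment is decided after randomisation and may depend on how they are recovering: a patient doing poorly may look for more therapy, and so may a well-motivated one. If such patients are dropped, those left at follow-up are a selected group. If the selection differs between arms, the FMA-UE contrast is no longer a comparison of randomised groups.

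Most of the 14 weeks lies after the intervention, so the two later visits are the most exposed. Treatment first received after week 2 cannot affect the end-of-intervention comparison, and treatment first received after week 6 touches only the last visit. The rule also spends the dropout allowance on patients whose outcome could have been measured.

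**Working it through.** **1. Scope of the rule**

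| Question | What the protocol article gives | Status |
|---|---|---|
| Is it separate from withdrawal? | Listed as its own item | Stated |
| Is it limited to weeks 1 and 2? | No limit; the neighbouring discontinuation rule has one | Not settled |
| Does ordinary rehabilitation count as other? | Part of every arm's care, no end stated; marked only in weeks 1 and 2 in Table 1 | Not settled |
| Are dropouts left out of the analysis? | Sample size raised because dropouts are expected not to contribute; the Statistical analysis section names no rule on keeping or excluding them | Implied |

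Table 1 also marks "Eligibility screen" at both follow-up visits. This is weak support for a rule that runs past week 2, because the inclusion and exclusion criteria contain nothing about later therapy.

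**2. The plan's own sample size**

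Inputs from the Sample size calculation section: three groups, means 8.11, 6.87 and 17.62, SD 8.83, alpha 0.025, power 0.90.

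- Grand mean: (8.11 + 6.87 + 17.62)/3 = 10.867.
- Sum of squared deviations: 7.599 + 15.973 + 45.608 = 69.180.
- Divided by the variance: 69.180/8.83² = 69.180/77.969 = 0.8873.
- Noncentrality with n per arm: λ = 0.8873n.
- Power = P(F′ > F crit), where F′ is noncentral F with 2 and 3(n − 1) degrees of freedom and noncentrality λ.

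At n = 18, λ = 15.97, the critical value is 3.969 on 2 and 51 degrees of freedom, and power is 0.902. At n = 17 power is 0.881. So 18 per arm (54 in all) reproduces. Then 18/0.80 = 22.5, rounded up to 23 per arm, and 3 × 23 = 69 reproduces too. The sample size arithmetic is not in question.

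**3. The allowance**

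23 − 18 = 5 per arm; 69 − 54 = 15; 15/69 = 21.7%. This covers every dropout reason together.

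**4. Power by number lost, for scale only**

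| Lost per arm | n per arm | Power, alpha 0.025 | Power, alpha 0.05 |
|---|---|---|---|
| 0 | 23 | 0.966 | 0.983 |
| 5 | 18 | 0.902 | 0.945 |
| 6 | 17 | 0.881 | 0.931 |
| 7 | 16 | 0.855 | 0.914 |
| 9 | 14 | 0.791 | 0.868 |

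The second alpha is the one given in the Statistical analysis section. The loss counts beyond 5 are assumptions, and they stand for losses from any cause. The table also assumes that the planning means and SD hold at follow-up; the sample size section names no visit.

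**The case against.** The strongest reply is that this is an undefined phrase in a condensed article, and that a full protocol or SAP may give the window and the handling. Harm needs three steps, none of them stated: the rule runs past week 2, the later treatment counts as other, and a dropout is no longer assessed or analysed. The item stands next to incomplete delivery of the treatment plan, so a treatment-period reading is natural. No item in the list carries a time limit, so its absence here may be only the style of the list. Since conventional rehabilitation belongs to every arm, other treatment most naturally means something else. Table 1's marks for conventional therapy sit in its intervention block and do not forbid later therapy.

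Much of this stands. A reader might infer that anyone who continues rehabilitation after week 2 is excluded and that the follow-up results are therefore biased. The document does not support that: coverage of ordinary rehabilitation and exclusion from analysis are both inferences, and no unequal uptake between arms is shown. A reader might also take the power table as the cost of this rule, which it is not.

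The reply does not dispose of the point, because the article states a rule rather than leaving one out. Receiving other treatment is made a reason for dropout, apart from withdrawal, in a plan that expects dropouts not to contribute. Removing assessable randomised patients for it is a poor rule even if it is confined to the two treatment weeks.

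**Conclusion.** The point holds in limited form. As worded, the criterion allows randomised patients who could still be assessed to be lost from the FMA-UE comparison for something they did after randomisation, with the two follow-up visits most exposed. That rests on reading dropout as the sample size section uses it, as a patient who no longer contributes.

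Its size cannot be derived. The document gives no basis for how many patients would be removed or for the direction of any bias. If uptake of other treatment and its link to recovery are the same in all three arms, the expected bias in the group contrast is about 0. On precision, the plan keeps its 0.90 power at alpha 0.025 up to 5 losses per arm from all causes and falls just below it at 6 (0.881).

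This should be changed because the correction is cheap, not because serious harm has been shown. Confidence is medium, since the wording leaves the scope open.

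**What to change.** Remove other treatment from the dropout reasons. State that receiving it, including ordinary rehabilitation after week 2, is not a reason to stop assessment or to exclude a patient. Assess these patients at all scheduled visits and analyse them in their randomised group. At the existing visits, record whether other treatment was received and of what type, including any further brain stimulation. Use the record for a description by arm and a sensitivity analysis.

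The cost is a sentence or two in the dropout criteria and one short item at visits already planned; no extra patients or visits are needed. The trade-off is that follow-up estimates will include any effect of later therapy, with some added noise and recall error in the treatment record.

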### Discontinuation criteria

If a patient develops other diseases or experiences serious adverse reactions during treatment, the trial will be discontinued at the mutual decision of the subject and the investigator.

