### ccPAS low frequency group

The affected side of the brain will receive dual-target transcranial magnetic stimulation with V1 and M1 as the target sites. The first coil will be placed above V1, tangent to the scalp, at a 45-degree angle to the midline; the second coil will be placed at M1, tangent to the scalp, also at a 45-degree angle to the midline. The stimulation of V1 will occur 18ms before that of M1 [45–47]. The daily ccPAS treatment protocol will consist of 180 pairs of transcranial magnetic stimulation pulses at a frequency of 0.2 Hz for 15 min [48]. The patients will receive the treatment while comfortably seated with relaxed extremities. The stimulation intensity will be set at 120% AMT, which is the minimum machine output intensity that elicits five MEP (motor evoked potential) amplitudes above 100 microvolts during mild contraction of the target muscle for 10 stimulations [49, 50]. MEP was recorded by stimulating M1 to induce contraction of the first dorsal interosseous(FDI) muscle.

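### The discontinuation rule makes a safety stop a joint decision of patient and investigator, and nothing in the article gives the investigator authority to stop stimulation alone

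*Protocol article*

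**What the plan says.** The section Discontinuation criteria consists of one sentence. Its trigger concerns an individual participant: "If a patient develops other diseases or experiences serious adverse reactions during treatment". Its consequence is that "the trial will be discontinued at the mutual decision of the subject and the investigator".

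The section just before it, Dropout criteria, lists four reasons for leaving: withdrawal, not completing the treatment plan, obtaining other treatment, and failure of the blind. A safety stop started by the investigator is not among them.

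Table 1 has a row labelled "Eligibility screen", assigned to Investigator B. It is marked before the study, in both treatment weeks and at the later visits. The article does not say what follows if a patient fails this screen during treatment.

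**The concern.** After a serious reaction to brain stimulation, the clinician responsible should be able to withhold the next session without needing anyone's agreement. The patient should be able to refuse it on the same terms. A rule that calls for a mutual decision gives neither of them that power in its own words.

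The patient loses nothing by this, since withdrawal is available separately. The investigator is the one left without a stated route, in the situation where medical judgement matters most: a patient has reacted badly, wants to continue, and has sessions remaining. The schedule makes this possible: "Each group will receive the intervention five times per week for two weeks".

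What is at stake is patient safety and clarity for the staff who apply the rule. No estimate or error rate is at stake.

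**Working it through.** No arithmetic applies. The plan states no figure on this point, and the question is what the rule allows and whether another section adds to it.

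**Step 1: apply the rule to the four possible positions after a serious reaction.**

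- Both want to stop: the rule is met and stimulation stops.
- Neither wants to stop: stimulation continues, as both intend.
- Only the patient wants to stop: the rule is not met, but the patient can withdraw under Dropout criteria.
- Only the investigator wants to stop: the rule is not met, and another route has to be looked for.

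**Step 2: look for that route in every section that deals with adverse events, leaving the study, delivery of treatment or oversight.**

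- Abstract, Method: adverse events are to be recorded. No action is attached to the record.
- Exclusion criteria: implants that rule out MRI or TMS, and past epilepsy, bar entry. The article thus treats fitness for stimulation as a safety matter, but these criteria govern entry and do not say who may stop treatment later.
- Dropout criteria: four reasons, none of them a stop by the investigator for safety. "Incomplete implementation of the treatment plan" describes an outcome and does not say who may bring it about.
- Table 1: the eligibility screen is repeated during treatment, with no stated consequence.
- Blinding: a designated researcher delivers stimulation at set parameters. No authority to halt it is mentioned.
- Data management: the hospital's clinical research management center supervises the data. No role in stopping treatment is given to it.

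**Step 3: result.** The fourth position in Step 1 has no stated resolution. The Discontinuation criteria section is the only one that addresses it, and it asks for agreement that, in this position, is absent.

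**Step 4: effect on the statistical design.** The sample size of 69, the alpha and the power do not depend on who may decide a stop. Nothing needs to be recomputed.

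**The case against.** The strongest reply is that silence is not prohibition. The sentence does not say that stimulation must continue until both agree, and no section obliges the person at the stimulator to deliver another session. A responsible clinician would very probably stop regardless. This is right, and it limits the point. A reader might infer that the article forbids the investigator to stop alone; the text does not support that. What stands is that the only stated rule asks for agreement and no section states an authority to act without it.

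A second reply is that other routes exist. The withdrawal entry under Dropout criteria does not say who may start it, and an eligibility screen repeated during treatment would have little purpose if failing it changed nothing. Both readings are possible, but each has to be supplied by the reader, and neither changes the sentence that deals with serious reactions directly.

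A third reply is that a journal article condenses a fuller protocol, which may hold the complete safety rules. That would answer a complaint about missing detail. Here the article did not leave the decision rule out: it printed one, and its wording is the difficulty. Translation may explain that wording but does not alter what it says.

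Two further readings are tempting and should not be adopted.

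- A reader might infer that one patient's reaction would end the whole study. The trigger is a single patient's event, so the word trial most plausibly means that patient's participation.
- A reader might infer that a patient stopped for safety becomes a dropout whose later FMA-UE assessments are lost. The article has separate headings for dropout and discontinuation, does not say that one leads to the other, and nowhere says that assessments cease. Whether such patients are followed is commonly left to the full protocol or analysis plan.

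**Conclusion.** The point holds in a narrow form. As worded, discontinuation after a serious adverse reaction or new disease needs the patient's agreement, and the article nowhere states that the investigator may stop stimulation alone.

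It is a minor point. It bites only when investigator and patient disagree in one direction, and the article gives no frequency for serious reactions or for such disagreement. No size in patients, sessions or bias is therefore claimed.

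The conclusion rests on two assumptions: that mutual carries its ordinary meaning of agreement by both, and that the printed sentence reflects the rule staff will follow. If the full protocol already gives the investigator sole authority, only the article's wording is at fault.

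**What to change.** Replace the sentence under Discontinuation criteria with:

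> After a serious adverse reaction or a new disease that makes stimulation unsafe, stimulation is stopped in that patient on the decision of either the investigator or the patient alone.

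This gives the investigator the missing authority and confirms the patient's own. It also limits the new-disease trigger to illness that bears on the safety of stimulation.

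The cost is one reworded sentence. It needs no additional patients, visits or committee. The downside is small: some patients who would have chosen to continue will be stopped.
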